**Fig. 1 f1:**
[figure not shown]
Project timeline. APSS, Assessment of Personality Strengths Scale; HADS, Hospital Anxiety and Depression Scale; PAQ-ICD-11-R, Personality Assessment Questionnaire for ICD-11 – Revised; PDS-ICD-11, Personality Assessment Schedule for ICD-11; PROMIS-SF, PROMIS-Short Form for Social Isolation; ReQoL, Recovering Quality of Life – 10 items; SAPAS, Structured Assessment of Personality – Abbreviated Scale; SSFQ, Short Social Functioning Questionnaire.

### Second assessment: three months after nidotherapy input to the first two villages

The SSFQ, PROMIS and ReQoL assessments will be completed for all participants.

*Third assessment: 6 months after completion of baseline assessment and after nidotherapy input to the second two villages*

The SSFQ, PROMIS and ReQoL assessments will be completed for all participants.

*Fourth assessment: 9 months after completion of baseline assessment and after nidotherapy input to the last two villages.*

All the assessments at baseline will be repeated, together with satisfaction scales, including an adverse event scale derived from the work of Klatte et al^
35
^ to determine the nature of adverse events in either arm of the trial. Satisfaction with the village environment will be recorded as a general statement at all assessments and satisfaction with the interventions also assessed using an agreed scale.^
36
^

A record of the most positive and negative environmental events^
37
^ will be made at the termination of the trial and linked to the cost-effectiveness analysis.

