## Research objectives

The primary objective of the trial is to determine if nidotherapy given in a whole community setting is more effective in improving social function than a mere demonstration of nidotherapy principles in other whole communities. The secondary objectives are to determine if nidotherapy also improves depressive and anxiety symptoms, quality of life, personality functioning and satisfaction with care to a greater extent than just demonstration of principles. We also wish to determine if nidotherapy is cost-effective by recording all the costs associated with its administration.

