## Method

The trial design is a cluster-randomised controlled trial using a step-wedge design of nidotherapy to be given to all adult residents (18 or over) in six villages in Nottinghamshire in central England. The plan is to randomise the six villages into three clusters each containing two villages, with active nidotherapy being given to each cluster for a period of 3 months. As the project will explain the principles of nidotherapy from the start of the study, when the people in villages are not receiving active nidotherapy, they will represent an unexposed passive nidotherapy control population.

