### Statistical design

The trial will use a randomised clustered step-wedge design with two arms. In the first 3-month period, the residents in all villages will be assessed to evaluate their clinical status and their environmental wishes. After 3 months a short check will be made on any material changes since recruitment. Two randomisations will then be carried out in three steps over 1 year. After the first 3 months of baseline assessment, two of the villages will be independently randomised to receive nidotherapy, with the other four acting as unexposed controls. At 6 months, another two villages from the remaining four will be randomised to nidotherapy with the last two unexposed villages as controls; at 9 months these remaining two villages will receive nidotherapy. Thus, the two villages receiving nidotherapy at first randomisation will have three 3-month periods to observe the post-treatment effects, the second two will have two periods to observe the post-treatment effects and the last two villages will have nidotherapy completed 12 months after the trial starts, and a final follow-up will take place for all participants within the following 3 months, and at 6 and 9 months environmental and short clinical assessments will be repeated on all participants.

The analysis will be carried out using intention-to-treat together with imputation of missing data. Analysis will be separated into three components: (a) change in scores of the primary outcome (social function); (b) change in scores of all secondary outcomes, including costs; and (c) changes in environmental satisfaction. Comparison in mean changes of outcomes between the two groups will be conducted using random effects models or multilevel models under a generalised linear modelling framework. Multilevel models^
23
^ will take into account both cluster effects of villages and difference among individuals, while estimating intervention effects over time. Considering that participants are not being randomised into treatment groups, refined models to assess intervention effects could adjust for baseline measures and other possible confounders.

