### Assessments

#### Baseline

All participants will receive a baseline assessment to determine eligibility and agreement to take part in all parts of the trial. This will be preceded by publicity from local news outlets.

Each of the participants agreeing to take part will complete the following assessments, deliberately chosen to be relatively short and easy to complete in all groups:the Short Social Functioning Questionnaire (SSFQ),^
25
^ a short version of a well-tested measure;^
26
^
the Structured Assessment of Personality – Abbreviated Scale (SAPAS);^
27
^
the Assessment of Personality Strengths Scale (APSS);^
28
^
the Hospital Anxiety and Depression Scale (HADS);^
29
^
the Personality Assessment Questionnaire for ICD-11 – Revised (PAQ-11-R);^
30
^
the Recovering Quality of Life (ReQoL) (10-item version);^
31
^
the Personality Assessment Schedule for ICD-11 (PDS-ICD-11);^
32
^
the PROMIS-Short Form for Social Isolation (PROMIS-SF) (a four-item scale for social cohesion) at initial and last assessment;^
33
^
a satisfaction scale and the SSFQ^
25
^ will be completed at the last assessment.

These data will be help to create a combined assessment of personality, with the Structured Personality Assessment from Notes and Documents (SPAN-DOC)^
34
^ tool.

These assessments will be made at interview and or by self-completed paper records immediately stored at a data protected facility to ensure confidentiality. These data will represent a mental health profile of each resident at each stage of the study.

Details of all nidotherapy actions will be recorded to establish the total costs of interventions.

After 3 months of initial data collection a short check will be made on any material changes since early recruitment. Two of the villages will then be randomised to nidotherapy independently by [name] (Fig. 1).

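### HADS and the personality scales are scheduled only when no village, or every village, has had nidotherapy, so their effect cannot be separated from calendar time

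*Protocol article*

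**What the plan says.** The secondary objective (Research objectives) is comparative. It asks whether nidotherapy "improves depressive and anxiety symptoms, quality of life, personality functioning and satisfaction with care to a greater extent than just demonstration of principles". The Method section defines the comparator: while villages are not receiving active nidotherapy, "they will represent an unexposed passive nidotherapy control population".

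Statistical design sets the roll-out in three steps. In the first step, after baseline, "two of the villages will be independently randomised to receive nidotherapy, with the other four acting as unexposed controls". The second step, in month 6, moves one more pair to active treatment and leaves one pair as the comparator. The third step, in month 9, treats that last pair. The same section plans to compare mean changes between two groups and lists all secondary outcomes among the analyses.

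The instruments are set out under Assessments. The baseline battery includes HADS, four personality instruments (SAPAS, APSS, PAQ-11-R, PDS-ICD-11), SSFQ, ReQoL and PROMIS. For the second and for the third assessment the text is the same: "The SSFQ, PROMIS and ReQoL assessments will be completed for all participants". At the fourth assessment, after the last two villages have been treated, "All the assessments at baseline will be repeated, together with satisfaction scales". Satisfaction with the village environment is recorded every time. The other satisfaction scale is placed at the last assessment.

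**The concern.** A stepped-wedge trial separates treatment from time because, at some assessments, treated and untreated villages are measured together. An outcome that is skipped at those assessments loses this protection. What remains is an uncontrolled before-after change over about 9 months, to which the randomisation contributes nothing. Seasonal change, the effect of repeated testing and any secular trend would all be counted as nidotherapy.

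Anxiety, depression and personality status are named secondary outcomes in the Abstract, and HADS is the only anxiety and depression scale in the set. The analysis plan cannot repair this, because the missing control data are never scheduled for collection. Once the middle assessments have passed, they cannot be recovered.

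**Working it through.** The article states no figure on this point that could be reproduced. The check is whether the treatment effect is identifiable under each measurement schedule.

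**Inputs.** Six villages in three sequences of two (Statistical design), and four assessments with the instruments listed under Assessments.

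| Assessment | Villages exposed | Villages unexposed | HADS, personality scales | SSFQ, ReQoL |
|---|---|---|---|---|
| 1 (baseline) | 0 | 6 | yes | yes |
| 2 | 2 | 4 | not listed | yes |
| 3 | 4 | 2 | not listed | yes |
| 4 | 6 | 0 | yes | yes |

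**Identifiability.** Take a model with village effects, period effects and one treatment indicator. The information on treatment is the variation of that indicator left after removing village and period. For T assessments and six villages:

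residual SS = Σx² − T·Σ(village mean)² − 6·Σ(period mean)² + 6T·(grand mean)²

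- Assessments 1 and 4 (HADS, personality scales): 6 − 3 − 6 + 3 = 0. Rank is 7 for 8 columns. Without village effects it is 2 for 3 columns, again with residual SS 0, so random village effects do not help.
- Assessments 1 to 4 (SSFQ, ReQoL): 12 − 7 − 9.333 + 6 = 1.667. Rank is 10 for 10 columns.
- Assessments 1, 2 and 4, if one middle assessment were added: 8 − 4 − 6.667 + 3.556 = 0.889. Rank is 9 for 9 columns. Assessments 1, 3 and 4 give the same.

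**Size of the bias if period effects are left out.** There are three 3-month intervals between assessments 1 and 4. A drift of d per interval appears as an effect of 3d. The document gives no drift, so d is assumed: 0.05 SD gives 0.15 SD, and 0.1 SD gives 0.3 SD.

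**Precision if HADS is taken at all four assessments.** Assumptions, none of them from the document: outcome variance 1, ICC ρ of 0.02 or 0.05, cluster autocorrelation 0.8, individual autocorrelation 0.6, and m participants per village. For village-period means:

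- variance V = ρ + (1 − ρ)/m
- covariance between periods C = 0.8ρ + 0.6(1 − ρ)/m

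For m = 50 and ρ = 0.02: V = 0.02 + 0.98/50 = 0.0396, and C = 0.016 + 0.6 × 0.0196 = 0.02776. Using within-village information alone, SE = √((V − C)/1.667) = √(0.01184/1.667) = 0.084. Generalised least squares, which also uses the between-village information, gives 0.082.

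| m per village | SE, ICC 0.02 | SE, ICC 0.05 |
|---|---|---|
| 50 | 0.082 | 0.100 |
| 25 | 0.105 | 0.120 |
| 15 | 0.130 | 0.141 |

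The value m = 50 is the 300 eligible residents given under Study setting divided by six. It therefore means that everyone takes part and nobody is lost.

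**The case against.** **The schedule may be wider than the list suggests.** Statistical design mentions short clinical assessments at 6 and 9 months, the Baseline section speaks of a mental health profile at every stage of the study, and it describes the scales as "deliberately chosen to be relatively short and easy to complete in all groups". The legend of the timeline figure names all the instruments, but the figure itself was not available for this review. The text is also loose elsewhere: the Baseline section puts PROMIS at the first and last assessments, while the later text has it at the middle ones too. This stands as a reason to reconcile the passages. It does not remove the point, because the only text shown that names the instruments for the middle assessments omits HADS and every personality scale. If wider measurement was intended, that list is wrong and needs correcting.

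**The sequences still differ at the fourth assessment.** They differ in time since nidotherapy. That supports a comparison of early with late exposure, not of nidotherapy with demonstration only.

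**Personality scales may serve mainly to profile participants.** The Interventions section does use personality assessment to select environmental change, so two measurements may be enough for some scales. The comparative claim for personality functioning should then be dropped.

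**A reader might infer that the whole secondary objective, or the trial, lacks a control.** The document does not support that. ReQoL belongs to the same objective and is taken at all four assessments, as is SSFQ for the primary outcome. Satisfaction with the village environment is recorded throughout.

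**A reader might also count satisfaction with care as the same scheduling fault.** That is only partly fair. Satisfaction with an intervention has no natural counterpart in villages that have not received it, so the missing control is largely inherent.

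**Conclusion.** The point holds for anxiety and depression (HADS) and for personality (SAPAS, APSS, PAQ-11-R, PDS-ICD-11). Under the schedule as written, treatment and calendar period coincide completely for these outcomes. Neither the stated secondary objective nor the planned two-group comparison can be estimated for them. This follows from the roll-out and the instrument lists alone and needs no numerical assumption. It would change only if HADS and the personality scales are in fact taken at the middle assessments.

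The drift figures and the standard errors are illustrative. The standard errors treat the variance components as known, which is optimistic with six villages. The primary outcome stands outside this point. It should be settled before the second assessment.

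**What to change.** 1. Add HADS and one personality-functioning scale already in the set, for example PAQ-11-R, to the second and third assessments. Analyse them with the same stepped-wedge model as SSFQ, including period effects.
2. For any outcome left at two time points, withdraw the comparative claim and report before-after change as descriptive. Report satisfaction with care or with the intervention as a descriptive end-of-study result.
3. Reconcile the instrument lists for the middle assessments with the wording on short clinical assessments (Statistical design), the profile at each stage (Baseline) and the timeline figure.

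The cost is a few more minutes of questionnaire time at two assessments already planned for all participants, and a small amendment. If that burden is not acceptable, step 2 alone removes the unsupported claim, at the price of having no controlled result for anxiety, depression or personality.

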Examples of the changes achieved in nidotherapy range from community ones to improve social isolation to employment interventions, improving local amenities, help in relationships and bigger changes such as a change of housing arrangements. The main advantage of community involvement is joint decision-making between members of the village, allowing shared benefits to be attained. If nidotherapy is embraced across the village, further benefits could be achieved. In many studies of desired interventions, equipoise is not present. In this study, because we have no previous data, equipoise is achieved, as it is quite possible that residents in the villages may be discomfited by assessments of their mental health and satisfaction, and view any attempts at intervention as interference in the smooth life of the village. The population being studied is not a typical one and is unlikely to be representative of the population with respect to mental health, even though suicide rates are higher in rural than urban areas. However, it has the advantage of being a relatively stable population whose circumstances are normally unchanging in the short term.

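### The only scheduled adverse-event scale is given once, after all six villages have had nidotherapy, although it is meant to describe events in both arms

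*Protocol article*

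**What the plan says.** The protocol article sets out the roll-out under Statistical design. After the baseline period, "two of the villages will be independently randomised to receive nidotherapy, with the other four acting as unexposed controls". The second step, three months later, is described as "another two villages from the remaining four will be randomised to nidotherapy with the last two unexposed villages as controls". The third and last step reads "at 9 months these remaining two villages will receive nidotherapy".

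The instruments are listed by visit in the assessment schedule. For the second assessment, and again for the third, the entry is "The SSFQ, PROMIS and ReQoL assessments will be completed for all participants"; no adverse-event measure is named. The fourth assessment is timed "9 months after completion of baseline assessment and after nidotherapy input to the last two villages". There the baseline battery is repeated and satisfaction scales and an adverse-event scale are added, the last of these "to determine the nature of adverse events in either arm of the trial". The scale is not in the list under Baseline.

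The one other mention of adverse events is a general statement in the Results paragraph of the Abstract that they will be recorded. It gives no time point, method or reference period. By contrast, the paragraph that introduces the adverse-event scale says explicitly that satisfaction with the village environment is taken at every assessment.

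**The concern.** The stated purpose refers to both arms, but at the only visit where the scale is placed there is one condition: every village has had nidotherapy. The second and third assessments already reach all participants while control villages exist, and the scale is not listed at either.

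This matters because the article treats harm as an open question. Its argument for equipoise, under Nidotherapy villages, is that "residents in the villages may be discomfited by assessments of their mental health and satisfaction, and view any attempts at intervention as interference". That sentence names two sources of possible harm: being assessed, which happens in every village from the start, and being offered an intervention, which happens only after a village crosses over. Separating the two, and separating both from ordinary life events, calls for adverse-event data from unexposed villages over the same calendar time. The scale as scheduled gathers none. Once the second and third assessments have passed, such data can no longer be collected prospectively.

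**Working it through.** No sample size, power or error rate is involved, so there is no figure in the article to reproduce. The check is a count of exposure at each visit, followed by a check of what can be estimated.

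**Inputs.** From Statistical design: six villages, two starting nidotherapy at each of months 3, 6 and 9. From the assessment schedule: the third and fourth assessments fall 6 and 9 months after baseline is complete. I take the second to be 3 months after it, which agrees with the repeat assessments at 6 and 9 months in Statistical design. With baseline complete at month 3, the visits fall at months 3 + 3 = 6, 3 + 6 = 9 and 3 + 9 = 12.

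**Exposure at each visit.** Unexposed villages = 6 − villages already started.

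| Assessment | Month | Exposed | Unexposed | Adverse-event scale listed |
|---|---|---|---|---|
| Baseline | 0 to 3 | 0 | 6 | no |
| Second | 6 | 2 | 6 − 2 = 4 | no |
| Third | 9 | 4 | 6 − 4 = 2 | no |
| Fourth | 12 | 6 | 6 − 6 = 0 | yes |

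**What the scale can estimate, as scheduled.** Take village-level adverse-event scores at the fourth assessment, modelled as intercept + b × exposure. Exposure is 1 for all six villages, so its column equals the intercept column. The design matrix has rank 1 for 2 parameters and b cannot be estimated. This treats the score as belonging to each village's exposure status at that visit.

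**What retrospective assignment would need.** The alternative is to ask at month 12 about earlier periods. Unexposed time ended at month 3, 6 or 9 according to starting order, which is 12 − 3 = 9, 12 − 6 = 6 or 12 − 9 = 3 months before the visit. Control-period events would therefore have to be recalled from at least that far back. Statistical design also allows the final follow-up to fall within the 3 months after month 12; at month 15 the intervals become 12, 9 and 6 months. They follow from the visit dates alone and assume nothing about how the scale is worded.

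**With the scale at the second, third and fourth assessments.** The exposed/unexposed splits are 2/4, 4/2 and 6/0. A model with three period effects and one exposure effect has 4 parameters, and its design matrix has rank 4, so the contrast can be estimated. Unexposed village-assessments number 4 + 2 + 0 = 6, against 0 as written. They come from 4 distinct villages, because the last two villages to start are counted at both visits.

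**The case against.** The strongest defence has four parts.

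*The scale may not be the only source of adverse-event data.* The Abstract's promise to record adverse events has no time limit, and Ethical aspects lets an investigator withdraw a participant for health reasons at any time, which suggests some attention to harm between visits. An article may leave a running log to the full protocol, and the timeline figure is not available. This stands as far as it goes: other recording cannot be excluded. But the article does more than omit detail. It states a schedule for the instrument and a purpose for it, and the two do not fit. The general sentence gives no method or timing that repairs this.

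*A dated recall over the whole trial could assign events to control time.* That is possible in principle, and the scale's reference period is not given. A reader might therefore go too far in inferring that adverse events cannot be compared between conditions at all, or that recall length differs by randomised order. The second inference holds only if each participant is asked about the time since their own nidotherapy began, which the article does not say; if all were asked about the whole trial, the window would be the same for everyone. What remains is that no recall window or event dating is stated, and that control time always precedes exposed time within a village, so fading recall would bear more heavily on control periods.

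*The purpose is descriptive.* The wording concerns the nature of events, not a comparison of rates, and Research objectives contains no safety comparison. This is fair, and it lowers the stakes. Even so, describing events under the control condition needs information from that condition.

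*Other controlled measures could show worsening.* Social function, PROMIS and ReQoL, together with environment satisfaction, are collected at the second and third assessments with 4 and then 2 control villages. It would therefore be wrong to infer that the trial is blind to harm while controls exist. These are not adverse-event measures, however, and do not show what kind of event occurred.

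**Conclusion.** The point holds in a limited form. The one adverse-event instrument that the article schedules is given when 0 of 6 villages are unexposed, and it is not listed at the two visits with 4 and 2 unexposed villages. It therefore yields no concurrent control data, and describing events in the control condition would rest on recall from at least 3 to 9 months earlier with no stated window or dating.

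This assumes that the visit lists in the article are complete for this scale and that villages cross over as Statistical design describes. The article does not support the reading that comparison is impossible under any form of recall, or that no other recording of harms exists.

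Severity is moderate. The primary outcome, the randomisation and the main analysis are untouched. The gain from correcting the schedule is real but modest, since the 6 added unexposed village-assessments come from only 4 villages.

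**What to change.** Give the same adverse-event scale to all participants at the second, third and fourth assessments, with a reference period of since the last assessment (about 3 months; for the second assessment, counted from the close of baseline). Report events by village-period, classed as unexposed, active nidotherapy or post-nidotherapy. State whether adverse events are also logged between visits and, if so, how and with what dates.

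The cost is a slightly longer questionnaire at two assessments that already take place for all participants, plus a small amendment.

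If the scale is to stay at the fourth assessment only, remove the reference to both arms from its stated purpose, give its recall window, and describe the adverse-event data as uncontrolled.
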